## 2. BACKGROUND

### 2.1 SARS-COV2 a novel respiratory virus causing a pandemic

In December 2019, a first series of severe respiratory infections caused by a rapidly spreading virus was reported from China, and the responsible virus was defined as a novel enveloped RNA betacoronavirus termed *severe acute respiratory syndrome coronavirus 2* (SARS-COV-2), with the associated respiratory illness referred to as COVID-19. Based on the current knowledge, SARS-COV-2 is a highly contagious virus transmitted human-to-human via droplets from nose/mouth due to its high concentration in fluids of the respiratory tract, but the way of transmission is not yet fully understood and particularly aerosol and surface stability are currently under investigation. In terms of clinical course, the symptoms are variable and range from asymptomatic cases to mild respiratory infections with cough, dyspnea and fever as leading symptoms, to pneumonia and severe acute respiratory distress syndrome (ARDS) with fatal consequences. Particularly elderly patients and patients with (multiple) chronic diseases such as cardiovascular diseases and diabetes have been identified as main risk groups for fatal events and are at risk for early need of intensive care and respiratory support. The estimated mortality rates range between <3% in the overall population to 10% in elderly patients and 40% in critically ill patients. Therapeutic approaches for COVID-19 are currently mainly empirical, and rapidly developed guidelines recommend supportive care-only in mild cases while severe cases are treated arbitrarily with previously active antiviral compounds such as HIV protease inhibitors lopinavir/ ritonavir, favipavir, remdesivir or anti-malaria drug hydroxychloroquine aiming to reduce the viral load. However, while particularly the latter agent in combination with the oral macrolide antibiotic azithromycin has shown first positive data in a small series of 20 patients, there is currently no stringent evidence-based treatment recommendation.

As of March 2020, more than 370,000 cases and 16,000 deaths have been confirmed worldwide and the WHO has classified the situation as a pandemic outbreak and global health emergency situation with the focus of new cases currently transferred to Europe. The rapidly increasing number of new infections results in a critical situation as many patients require intensive care and invasive ventilation which currently constitutes the main limiting factor in effectively caring for these patients. Thus, finding new therapeutic strategies and ways to limit spread of the disease but also mitigation measures to ensure a less aggressive clinical course in patients tested positive for COVID-19 are of utmost importance.

## 2.2 COVID-19 in cancer patients

Patients with an active diagnosis of cancer are prone to infections for multiple reasons, ranging from a potentially compromised immune system due the disease itself, tumor cachexia and malnutrition, to immunosuppression as the main side effect of most cancer treatments such as chemotherapy, molecular targeted agents and immunotherapy. A first analysis of a nation-wide cohort of 1590 COVID-19 patients in China identified 18 patients with a history of malignancy and sufficient medical data for detailed analysis , and reported an extrapolated three-fold higher rate of cancer patients within this collective if compared to the normal population (1% versus 0.29%). Furthermore, this analysis documented a significantly higher risk to develop severe symptoms, defined as the percentage of patients admitted to the intensive care unit requiring invasive ventilation or death, if compared to the overall population (39% vs 8%,  $p=0.0003$ ). At particular high risk were patients with active treatment, with three of four patients undergoing antitumor therapy categorized as severe cases. Finally, the authors also reported a more rapid course of the disease with the median time to serious events being 13 versus 43 days ( $p<0.0001$ ). While the numbers in this cohort are limited, these data clearly suggest cancer patients and particularly patients with ongoing treatment as a high risk group for severe COVID-19 manifestations. Whereas additional large cohorts on cancer patients are still lacking, this series identified age, lymphopenia and leucopenia but also concurrent treatment with prednisone as strong predictors of ARDS development and severe clinical course, with all of these factors being relevant in cancer patients . In response to this, Onkopedia , a consensus platform for oncological care in German-speaking countries, has already prompted a specific guideline for managing cancer patients during the COVID-19 pandemic and suggested specific decision criteria for triaging application of anticancer treatments in view of infection risk and underlying cancer disease status.

## 2.2 Azithromycin: Background

Macrolide antibiotics are a class of antimicrobial compounds commonly used for a wide range of community acquired but also atypical infections targeting a broad spectrum of cocci bacteria, gram negative rods and atypical pneumonia pathogens. Beside their use as antibacterial agents, they have recently become a focus of interest in the context of “drug repurposing” in oncology and pulmonology due to pronounced immunomodulatory effects and direct antiproliferative features . The suggested underlying mechanisms are mainly based on an increase in CD8+ cells, NK cells and interferon-gamma producing T-cells; furthermore macrolides decrease VEGF and TNF-alpha levels and act modulating on the release of

various cytokines including interleukins (IL) 6 and 8 . Effects also include more specific mechanisms like alterations of the mTOR pathway . In terms of clinical antitumor efficacy, clarithromycin showed activity in Waldenstrom's disease, multiple myeloma and more recently in mucosa-associated lymphoid tissue (MALT) lymphoma, a disease highly dependent on the tumor microenvironment and related to infectious diseases . In two phase II trials and one large retrospective series, excellent tolerance and objective durable responses in 50% of patients were reported, and evaluation of the concept is ongoing . Furthermore, azithromycin as long-term single agent once weekly (1500 mg) was evaluated for MALT lymphoma, and while the tumor response rate was inferior to clarithromycin at only 25%, tolerance and compliance were excellent, with no relevant adverse effects reported . In spite of the fact that azithromycin appears to be less effective than clarithromycin in MALT lymphoma, the study showed stable drug-concentrations over the whole duration of therapy with excellent tolerance of 1500 mg (3 x 500 mg on a single day) weekly. The compound has also shown a broad range of immunomodulatory applications with established efficacy and clinical routine use in a variety of chronic lung diseases including obstructive pulmonary disease, cystic fibrosis, bronchiolitis obliterans syndrome or asthma .

In the current era of the COVID-19 pandemic, azithromycin is of therapeutic interest, and while it was initially only suggested as possible treatment for bacterial superinfection in severe COVID-19 cases, a highly featured article has reported that the antiviral effects of the anti-malaria compound hydroxychloroquine could be augmented by addition of azithromycin . In these preliminary results of a small phase II trial, azithromycin was allowed as add-on to hydroxychloroquine 600 mg daily if clinically indicated (number of treated patients = 20). At day 6 post inclusion, no viral load was detectable in 70% of patients versus in 12.5% in the control group ( $p=0.001$ ), and if results were further divided into patients receiving hydroxychloroquine alone or plus azithromycin, the rate of virological cure was 100% for the combination versus 57.1% for the hydroxychloroquine-only group. Differences in these outcomes were observed as early as from day 3 . While the reasons for these effects of azithromycin are not fully understood and need to be further investigated, a further recent publication evaluating inflammation patterns in lung allograft recipients reported that prophylactic treatment with azithromycin was able to reduce the production of inflammatory cytokines but also to decrease the replication of human rhinovirus , suggesting substantial anti-viral effects due to pretreatment with this pleiotropic compound.

## 2.3 Rationales for performing the study

COVID-19 disease constitutes a global threat with a particular danger for immunocompromised individuals such as cancer patients undergoing active treatment with chemotherapy with an increased risk of infection and devastating mortality rates up to 40% on top of the already reduced life expectancy of cancer patients. The macrolide antibiotic azithromycin has been shown to be effective for active and prophylactic treatment of respiratory infections and was additionally proven to not only act as an immunomodulator for the treatment of chronic lung diseases and but also appears to decrease viral replication in allograft lungs and potentially also in SARS-COV2 infected patients. Furthermore, azithromycin has a relatively good bioavailability and shows no significant side effects if applied long-term at a regular dose, e.g. 1500 mg per day once weekly as evidenced in the pilot trial of azithromycin for MALT lymphoma, while application of hydroxychloroquine may result in relatively severe toxicities. In view of these observations, we hypothesize that oral application of azithromycin 1500 mg orally once a week could effectively improve outcome of cancer patients undergoing antineoplastic treatment during the COVID-19 pandemic.

## 3. STUDY DESIGN AND OBJECTIVES

### 3.1 Study design and endpoints

**Study design:** This is a single-blinded, placebo-controlled, randomized, single center study to evaluate the capacity and safety of oral azithromycin as prophylactic treatment in cancer patients undergoing antineoplastic therapy including conventional chemotherapy +/- antibodies (bevacizumab, cetuximab, rituximab and obinotuzumab) or checkpoint-inhibitors. In this trial, patients will be randomized to azithromycin monotherapy orally once weekly at a dose of 1500 mg (3 x 500 mg taken on one day) versus standard of care with continued antineoplastic therapy only. Treatment will last for a maximum of 8 weeks in the absence of demonstrated infection with SARS-COV2.

#### Primary endpoints:

- Cumulative number of SARS-COV-2 infections as verified by PCR from routine nasal swabs performed every 28 days (symptomatic or asymptomatic) at week 12 after initiation of therapy

**Secondary endpoints:**

- To evaluate the capacity of azithromycin to prevent severe COVID-19 infections, defined as a combined endpoint of hospitalization and death in cancer patients undergoing active treatment with chemotherapy
- Severity of COVID-19 cases (see grading as defined by the WHO)
- All-cause mortality
- Safety and tolerability of IMP (clinical and laboratory, CTCAE criteria)
- Occurrence of viral or bacterial infections other than COVID-19
- Development of azithromycin-resistant bacterial strains as assessed by nasal swabs

#### 4. STUDY DURATION

**Duration of the study:** 5 months

**Recruitment period:** 2 months

**First patient in:** April 25, 2020

**Last patient out:** August 25, 2020

#### 5. NUMBER OF PATIENTS AND SELECTION CRITERIA

##### 5.1 Total number of patients

A total number of 200 patients (100 patients in each arm) is planned for enrollment in this pilot trial. For statistical considerations and sample size calculation see section on Statistics.

##### 5.2 Inclusion criteria

To be included each patient must fulfill all of the following criteria:

- Histologically confirmed cancer diagnosis
- Active disease in need of antineoplastic therapy
  - o treatment may include classical cytostatic agents, molecular targeted therapy, monoclonal antibodies bevacizumab, cetuximab, rituximab and obinutuzumab (either alone or in combination with chemotherapy) and checkpoint inhibitors
  - o treatment may be ongoing or newly started
  - o oral, intravenous or subcutaneous application route is allowed

- adjuvant, neoadjuvant or palliative chemotherapy is allowed
- the planned treatment duration must be at least 3 months, i.e. 12 weeks
- Age  $\geq 18$  years
- Life expectancy of at least 3 months
- Adequate renal, cardiac and liver function to tolerate the treatment
- Normal QTc ( $\leq 450$  ms) on ECG
- ECOG performance status of  $< 3$
- Negative PCR for SARS-COV-2 not older than 28 days
- Capable of understanding the study and giving informed consent

### 5.3 Exclusion criteria

Patients who fulfill any of the following criteria will be excluded:

- Active COVID-19 as defined by clinical WHO criteria and a positive PCR for SARS-COV2
- Use of any investigational agent within 28 days prior to study start
- Ongoing radiotherapy
- A history of uncontrolled seizures, central nervous system disorders or psychiatric disability judged by the investigator to be clinically significant and adversely affecting compliance to study drugs
- Clinically significant cardiac disease including unstable angina, acute myocardial infarction within six months prior to randomization, congestive heart failure (NYHA III-IV), arrhythmia unless controlled by therapy, with the exception of extra systoles or minor conduction abnormalities,
- long QT syndrome (QTc interval  $>450$ ms).
- Subjects who have current active hepatic or biliary disease (with exception of patients with Gilbert's syndrome, asymptomatic gallstones, liver metastases or stable chronic liver disease per investigator assessment)
- Inadequate kidney function: serum-creatinine  $>2.0$  times upper normal limit
- Hepatic dysfunction: total bilirubin  $>1.5$  times upper normal limit (unless due cancer involvement of liver or a known history of Gilbert's disease); ALT  $>2.5$  times upper normal limit (unless due to disease involvement of liver); alkaline phosphatase  $>2.5$  times upper normal limit (unless due to disease involvement of the liver or bone marrow)
- Patients with active opportunistic infections
- Pregnant or lactating women. Women of childbearing potential must have a negative pregnancy test at screening, pregnancy testing must be performed within 7 days of administration of IMP. Approved methods of birth control must be used

- Women of childbearing potential, including women whose last menstrual period was less than one year prior to screening, unable or unwilling to use adequate contraception from study start to one year after the last dose of protocol therapy. Adequate contraception is defined as hormonal birth control, intrauterine device, double barrier method or total abstinence.
- Male subjects unable or unwilling to use adequate contraception methods from study start to one year after the last dose of protocol therapy
- Hypersensitivity to azithromycin or other macrolides
- Concurrent medication with ergotamine, theophylline or digitalis
- Inability to swallow tablets/study medication

## 6. OUTCOME PARAMETERS

### 6.1 Definition of the primary endpoint

Number of SARS-COV-2 infections (symptomatic or asymptomatic): detected by routine SARS-COV-2 tests in all patients treated at the Division of Oncology, Medical University of Vienna. During the SARS-COV-2 pandemic, the routine approach to patients undergoing chemotherapy at our institution is PCR from nasal swabs taken every 28 days. The cumulative number of infections detected (symptomatic or asymptomatic) at week 8 after initiation of therapy in both treatment arms serves as the primary endpoint.

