|                                      | 
 
- QTc <math>\leq</math> 450 ms
 
- ECOG performance status of <math>< 3</math>
 
- Capable of understanding the study and giving informed consent
 
- Negative COVID-19 test at study entry as measured by routine testing (not older than 28 days)
 
                                                                                                                                                                                                                     |
| EXCLUSION CRITERIA (SYNOPSIS) | 
 
- Use of any investigational agent within 28 days prior to study start
 
- Patients with active opportunistic infections
 
- Pregnant or lactating women
 
- Women of childbearing potential and male subjects not willing to use adequate contraception methods during the study period
 
- Hypersensitivity to azithromycin or other macrolides
 
- Concurrent medication with ergotamine, theophylline, digitalis
 
- Inability to swallow tablets
 
 |
| TEST DRUG (IMP) / TREATMENT   | 
Azithromycin, applied as long-term treatment at once weekly dose of azithromycin 1500 mg (i.e. 3 x 500 mg on one day) orally.
 
Patients will be randomized to azithromycin monotherapy given orally once weekly at a dose of 1500 mg versus placebo. Treatment will last for a maximum of 8 weeks in the absence of documentation of SARS-COV-2-infection.
                                                                                                                                                                           |
| PRIMARY ENDPOINT              | 
 
- Cumulative number of SARS-COV-2 infections (symptomatic or asymptomatic) as assessed by positive PCR from routine nasal swabs (performed every 28 days) at 12 weeks after initiation of therapy
 
                                                                                                                                                                                                                                                                                               |

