### 6.2 Definition of secondary endpoints

Number of patients experiencing severe COVID-19 infection defined as a combined endpoint of hospitalization or death at week 12 after initiation of therapy.

COVID-19 cases are defined as outlined by the WHO, including a PCR for COVID-19 from any specimen (respiratory, blood, urine, stool, other bodily fluids).

Severity of COVID-19 cases: The severity of cases will be classified as suggested in the Blue Print for COVID-19 therapeutic trials by the WHO (range 0-8)

**Table.** Ordinal Scale for Clinical Improvement of COVID-19 (WHO Blueprint).

| Patient state                 | Descriptor                                                  | Score |
|-------------------------------|-------------------------------------------------------------|-------|
| Uninfected                    | No clinical or virologically evidence of infection          | 0     |
| Ambulatory                    | No limitations of activity                                  | 1     |
|                               | Limitation of activities                                    | 2     |
| Hospitalized – mild disease   | Hospitalized, no oxygen therapy                             | 3     |
|                               | Oxygen by mask or nasal prongs                              | 4     |
| Hospitalized – severe disease | Non-invasive ventilation or high flow oxygen                | 5     |
|                               | Intubation and mechanical ventilation                       | 6     |
|                               | Ventilation + additional organ support – pressors, RRT, ECM | 7     |
| Dead                          | Death                                                       | 8     |

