## 8. STUDY PROCEDURES

### 8.1 Screening and eligibility

The Investigator is responsible for keeping a record of all subjects who sign an informed consent form (ICF) for entry into the study. All subjects will be screened for eligibility. Investigations at baseline and during the study are outlined below. Study Assessments, unless otherwise specified, must take place within 28 days prior to initiation of therapy. Screening pregnancy tests for women of childbearing potential must occur within 7 days before first application of investigational medical product (IMP). Before screening, a negative SARS-COV-2 PCR not older than 28 days must be present.

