## **9. PREMATURE WITHDRAWAL**

### **9.1 Premature trial termination**

Any patients who experience a serious adverse event may be withdrawn at any time from the study at the discretion of the investigator. If any serious disadvantage of the treatment becomes evident during the clinical trial, therapy will be terminated. In this case the necessary procedures will be arranged to ensure protection of the subjects' interests.

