## Primary Endpoint Analysis

All primary analyses will be on the ITT set and the analysis based on the per protocol set will be provided as supportive analysis. The primary endpoint is the between group difference in the incidence rate per 4 weeks. We will compute 2-sided 95% confidence bounds for the incidence rates. Furthermore, we test the null hypothesis that the incidence rates in the two groups are equal. To estimate and compare the incidence rates, the test status at weeks 4,8,12 will be modeled using time to event analysis models and will adjusted for calendar time to account for time trends in the incidence rate. The time-to-infection is defined as time from randomization to infection. If patients drop out, their observations will be censored at the last observation time.

This data will be visualized by Kaplan-Meier Plots. For each group unadjusted two-sided 95% confidence intervals will be reported as well.

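### The primary endpoint is worded around routine-care 28-day swabs, so infections found by other tests, or after routine swabbing stops, may go uncounted; separately, the qualifying negative test may be weeks old

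*Protocol*

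**What the plan says.** **Primary endpoint.** The synopsis counts infections "as assessed by positive PCR from routine nasal swabs (performed every 28 days) at 12 weeks after initiation of therapy". Section 3.1 agrees: "Cumulative number of SARS-COV-2 infections as verified by PCR from routine nasal swabs performed every 28 days". Section 6.1 speaks of infections "detected by routine SARS-COV-2 tests in all patients treated at the Division of Oncology, Medical University of Vienna", symptomatic or not, and then explains that "the routine approach to patients undergoing chemotherapy at our institution is PCR from nasal swabs taken every 28 days".

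**Other uses of a positive test.** Section 6.2 defines COVID-19 cases by the WHO criteria, "including a PCR for COVID-19 from any specimen". Section 8.4 acts on a positive PCR at any time during treatment.

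**Schedule.** Section 8.3 describes the 28-day SARS-CoV-2 PCR as routine care whose results the study will use. It is not among the listed baseline or on-study investigations, which run to end of treatment; the nasal swab listed there is for bacterial resistance. The primary analysis in Section 10.2 models test status at weeks 4, 8 and 12.

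**Leaving the study.** Section 9.1: "Any patients who experience a serious adverse event may be withdrawn at any time from the study at the discretion of the investigator". Section 11.2 makes inpatient hospitalisation a serious adverse event. Section 10.2: "If patients drop out, their observations will be censored at the last observation time".

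**Entry test.** The synopsis requires a negative test at study entry no older than 28 days. Section 5.2 sets the same limit without a reference date. Section 8.1 says: "Before screening, a negative SARS-COV-2 PCR not older than 28 days must be present". It also lets study assessments fall up to 28 days before therapy starts.

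**The concern.** These passages do not give one rule for what counts as a primary infection. Take a patient admitted with COVID-19 at week 6 and diagnosed by a hospital PCR. Section 6.2 makes this a severe case. Under the literal primary definition it is an event only if a routine swab is later taken and is still positive. If the patient dies, is withdrawn after the serious adverse event or stops attending, that swab may never happen, and the patient is censored at the last observation. Two analysts could count this patient differently.

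The week-12 result has a similar weakness. The analysis needs it, but no listed study procedure secures it, and an analysis plan cannot recover swabs that were never taken.

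The entry test raises a different problem. An old negative lets infections already present at randomisation be counted as failures of prophylaxis. That adds events to both arms; it does not hide any.

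**Working it through.** **Inputs from the Protocol (Section 10.1).** 100 patients per arm, two-sided level 0.05, rates of 50% and 30%. The Protocol gives no capture rate, no entry prevalence and no duration of PCR positivity, so those below are assumptions.

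**Formula.** Power = Φ[(|p1 − p2| − 1.96·SE0)/SE1], with SE0 = √[2p̄(1 − p̄)/100] and SE1 = √{[p1(1 − p1) + p2(1 − p2)]/100}.

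**1. The Protocol's own figures.** For 60% versus 40%: SE0 = 0.0707, SE1 = 0.0693, (0.20 − 0.1386)/0.0693 = 0.886, power 81.2% (stated: at least 81%). Confidence interval half-width: 1.96·√(2 × 0.25/100) = 0.139 (stated: 0.14). For the Protocol's example of 50% versus 30%, power is 82.8%. The arithmetic is sound, but it describes detected proportions and so takes detection as complete.

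**2. Equal under-capture.** Detected rate = c × true rate, true rates 50% and 30%.

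| Captured share c | Detected rates | Difference | Power |
|---|---|---|---|
| 100% | 50% vs 30% | 20 points | 83% |
| 90% | 45% vs 27% | 18 points | 76% |
| 80% | 40% vs 24% | 16 points | 68% |
| 70% | 35% vs 21% | 14 points | 60% |
| 60% | 30% vs 18% | 12 points | 51% |

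The ratio of the rates stays at 0.6 throughout. The absolute difference and the power are what shrink.

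**3. Could the counting rule favour one arm?** Suppose the drug prevents no infection and only shortens PCR positivity. With infections spread evenly over the swab interval, a 28-day swab detects a share min(1, D/28) when positivity lasts D days. The apparent reduction is one minus the ratio of the shares:

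- 20 to 18 days: 1 − 18/20 = 10%
- 20 to 14 days: 1 − 14/20 = 30%
- 30 to 24 days: 1 − (24/28)/1 = 14%
- 35 to 30 days: both shares are 1, so 0%

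These pairs are illustrations. The result depends entirely on the durations assumed.

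**4. Infections present at entry.** If a share q is already infected in both arms and is counted, the observed rate is q + (1 − q) × rate. With q = 5%: 0.05 + 0.95 × 0.50 = 52.5% and 0.05 + 0.95 × 0.30 = 33.5%, a difference of 19 points and power of 78%. With q = 2% power is 81%; with q = 10%, 73%.

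**5. Age of the qualifying negative.** It is 28 days by the synopsis and Section 5.2. If the two windows in Section 8.1 are added, it is 28 + 28 = 56 days at first dose.

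**The case against.** The strongest reply is that nothing in the Protocol expressly excludes other positives. Section 6.1 includes symptomatic infections and speaks of routine tests in all patients treated at the Division. Section 8.4 recognises positivity at any time. Section 9.2 treats withdrawal for infection in the first four weeks as a category of its own. The authors may well have meant to count every positive. That stands: the fault is an unreconciled definition, not a declared exclusion.

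It is also tempting to infer that patients who stop chemotherapy drop out of swabbing. The Protocol is silent on this. Section 5.2 requires at least 12 weeks of planned antineoplastic treatment, Section 10.1 gives 12 weeks of follow-up and the synopsis mentions an end-of-study visit. The routine should therefore reach week 12 for most patients. This limits the gap but does not close it, because planned treatment can stop early and no listed procedure then requires the test.

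A reader might go further and infer that the swab rule builds in a false benefit equal to the 30% activity threshold in the synopsis. The documents do not support that. The 30% arises from one assumed pair of durations; other pairs give 0% to 14%. The cited clearance data concern azithromycin added to hydroxychloroquine in infected patients. Even a spurious 30% reduction would reach significance with 200 patients in only about 12% of trials at a detected control rate of 10%, and 57% at 50%.

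Finally, a fixed swab schedule has a real merit. The trial is single-blinded, so discretionary symptom-triggered tests could differ by arm. That argues for a sensitivity analysis restricted to scheduled swabs, not for leaving diagnosed infections out of the main count.

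**Conclusion.** The point holds as a conflict in the endpoint definition and a gap in the schedule. The primary wording rests on routine 28-day swabs, while other sections accept positives from any specimen and at any time. A patient diagnosed between swabs can be a severe case and still be censored as uninfected. The week-12 test is needed by the analysis but is not a listed study procedure.

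The most direct cost is lost power: from 83% to 68% at 80% capture and to 51% at 60%, using the Protocol's planning test in place of its time-to-event model and assuming equal capture in both arms. Bias between arms is possible, through shortened positivity or outcome-related withdrawal, but the documents do not show it.

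The entry test is a separate, smaller matter. It dilutes the effect and does not cause missed outcomes; 5% prevalent infection takes power to 78%. A reader might take 56 days as the permitted age. It is only one reading of Section 8.1, and the synopsis points to 28 days at study entry. The passages need reconciling.

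**What to change.** 1. **Section 6.1.** Define the event as the first positive SARS-CoV-2 PCR from any specimen or source, with its date, from randomisation to the primary time point. Settle that time point at the same time: Section 6.1 says week 8, while the synopsis and Section 3.1 say week 12. Keep scheduled swabs alone as a sensitivity analysis.
2. **Section 8.3.** List the PCR at weeks 4, 8 and 12 for every randomised patient. State that PCR results continue to be collected after study drug or antineoplastic therapy stops, including after a serious adverse event, unless consent is withdrawn. The rules for stopping treatment stay as they are.
3. **Sections 8.1 and 5.2 and the synopsis.** Reconcile them so that the age of the qualifying negative is counted back from randomisation and, where possible, randomise soon after a routine swab.

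The cost is small: a few extra swabs in patients off routine care, sometimes a short wait before randomisation, and some dependence on symptom-triggered testing, which the sensitivity analysis addresses. The change recovers infections diagnosed elsewhere and swabs that would otherwise not be taken. It cannot recover infections that clear, untested, between two swabs.
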